## Abstract

**Background:**

Smoking cessation treatment programs have been widely available for patients with nicotine dependence. Despite intensive programs, the continuous abstinence rate (CAR) from weeks 9-12 is still about 50%. Recently, a smartphone app emerged as a novel tool for therapeutic interventions, including nicotine dependence. In this study, we developed “CureApp Smoking Cessation” (CASC), which consists of a smartphone app for patients and a Web-based patient management software for doctors with a mobile carbon monoxide (CO) checking device to improve the efficacy of the smoking cessation treatment.

**Objective:**

This study aims to evaluate whether the CASC app is effective for individuals with nicotine dependence in addition to standard smoking cessation programs.

**Methods:**

This will be a randomized, sham-controlled, open-label, multicenter trial. We will recruit participants with nicotine dependence, but are otherwise healthy adults. We will randomize and allocate participants 1:1 to the CASC treatment group or a control app group. Both groups will receive a 12-week standard smoking cessation program with pharmacotherapy and counseling. In addition, participants in the treatment group will have the CASC app installed on their smartphone, which will provide video tutorials, advice from an artificial intelligence nurse, a digital diary, and measure daily exhaled CO concentration. In contrast, the control group will have the control app installed on their smartphone, where all the functions that can potentially effect smoking cessation are removed. The primary outcome will be the biochemically validated CAR from weeks 9-24. The success of smoking cessation will be defined as self-reported continuous abstinence from weeks 9-24 and exhaled CO concentration ≤10 ppm both at weeks 12 and 24. The main secondary outcomes will be the CAR from weeks 9-12, weeks 9-52, and 7-day point prevalence abstinence at weeks 4, 8, 12, 24, and 52.

**Results:**

We will recruit 580 participants with nicotine dependence from October 2017 to September 2018 or until the recruitment process is complete. The final 52-week follow-up will be completed in October 2019. We expect all trial results to be available by the end of 2019. The trial is funded by CureApp, Inc.

**Conclusions:**

This is the first randomized controlled trial to evaluate the efficacy of CASC. We expect that CASC, in addition to standard smoking cessation programs, has a significantly higher CAR during weeks 9-24 than the control app.

**Trial Registration:**

University Hospital Medical Information Network Clinical Trials Registry UMIN000031589; https://upload.umin.ac.jp/cgi-open-bin/ctr/ctr_view.cgi?recptno=R000033555

**International Registered Report Identifier (IRRID):**

DERR1-10.2196/12252

## Introduction

Smoking is a risk factor that causes various diseases such as malignant tumors, heart disease, cerebrovascular disease, and chronic obstructive pulmonary disease [1]. It has been estimated that there are 22 million (approximately 18% of the total Japanese population) of adult smokers in Japan, and the number of deaths attributable to smoking is approximately 129,000 per year, indicating that smoking is the most common extrinsic cause of death among noninfectious diseases [2]. In addition, excess medical expenses owing to smoking are up to 1.5 trillion yen (US $13 billion) [3]. Therefore, reducing smoking prevalence could contribute to not only prevent the onset of these lifestyle-related diseases and cancer but also decrease future medical costs [4].

Smoking cessation treatment programs have been widely available for patients with nicotine dependence supported by the Japanese national insurance system [5]. This program consists of 5 visits spanning 12 weeks providing counseling by health care professionals and pharmacotherapy, including nicotine patch and varenicline. Despite this intensive treatment program, the continuous abstinence rate (CAR) from weeks 9-12 has still been 40%-65% [6-8]. Moreover, it significantly decreases after the program finishes and is around 40% at 1-year follow-up [7]. To improve both in-program and long-term CAR, we need additional and more effective treatment interventions both during the regular outpatient clinic visits and after the completion of the 12-week program [6].

Medical apps for smartphones are emerging as “therapeutic” intervention tools to ameliorate diabetes mellitus [9,10], depression [11], and nicotine dependence [12,13]. Because they cover interoutpatient visit blank periods (ie, intervals between clinic visits during which patients normally cannot obtain any clinical guidance from medical staffs), these apps are useful to continuously monitor, promote, and encourage the treatment program from medical staff, as well as by patients themselves. In this regard, Free et al [13] reported that smoking cessation support with daily or weekly text messages during the program doubled smoking quit rates. Although smartphone apps for nicotine dependence are already available in the United States, it remains unclear whether the app with a mobile carbon monoxide (CO) checker device is safe and effective in patients with nicotine dependence.

Recently, we developed “CureApp Smoking Cessation” (CASC), which consists of the latest version of CureApp Smoking Cessation smartphone app for patients and a Web-based patient management software for primary physicians with a mobile CO checking device to improve the success of the smoking cessation treatment. The CASC provides users with accurate knowledge of nicotine dependence, clues to change their behaviors, and measurements of their own exhaled CO concentration levels at home. In addition, patients can share these data remotely with their primary physicians. Masaki et al reported that, in the previous prospective studies with participants using prototypes of CASC smartphone app without a mobile CO checker, the results showed the feasibility and usability in the phase I study [14] and demonstrated a higher CAR from weeks 9­-24 than the national surveys in the phase II study [15].

Therefore, this study aims to evaluate whether the latest version of CASC in addition to a standard smoking cessation program is effective in treating individuals with nicotine dependence.

## Methods

### Overall Trial Design

Figure 1 shows the flowchart of the trial. This trial will be a randomized, sham-controlled, open-label, multicenter trial. Table 1 shows trial centers. This trial aims to assess the efficacy of CASC in patients with nicotine dependence when added to a standard smoking cessation program. The treatment group will use the CASC smartphone app integrated with a mobile CO checker and a Web-based patient management software for 24 weeks. Table 2 shows the overall follow-up schedule. The primary outcome of this study will be the CAR from weeks 9-24. We hypothesize that the CASC treatment group will have a higher CAR than the control app group from weeks 9-24. The CAR is defined as the percentage of individuals continuously not smoking even a puff during the specified period. We will conduct this trial in compliance with the Declaration of Helsinki, Medical Device Good Clinical Practice, Ethical Guidelines for Medical and Health Research Involving Human Subjects, and all other applicable laws and guidelines in Japan. This protocol and informed consent forms were approved by the Institutional Review Board at Keio University School of Medicine and affiliated institutions. Furthermore, we will use the latest version of the approved documents. This study is registered at the University Hospital Medical Information Network Clinical Trials Registry (UMIN000031589).

**Figure 1 figure1:**
[figure not shown]
Flowchart of the trial protocol. CASC: CureApp Smoking Cessation.

### Trial Participants

We will recruit nicotine-dependent adult participants from October 2017 to September 2018 or until the recruitment process completes; we plan to follow them until October 2019. Participants who meet all inclusion criteria will be included in the trial and those fulfilling the exclusion criteria will be removed from this trial (Textbox 1). We will obtain written informed consent from all trial participants. Participants should understand the content of the consent form sufficiently before their acceptance*.* Consent forms must be dated and signed both by trial participants and researchers. When consent is obtained, the first copy of the form will be kept in each institution, while the other part will be kept by participants and will not be collected even after the trial is over. In addition, we will inform all participants that their medical care will not be affected if they refuse to enroll in this trial. Participants will be able to leave the trial whenever they want to discontinue it. All participants will receive a compensation of 10,000 yen per clinic visit (7 visits in total).

### Randomization

Randomization will be performed for eligible participants. They will be allocated 1:1 to both arms—the CASC treatment group and the control app group. Randomization will be performed by a computer-generated random sequence with stratification for smoking cessation medications.

**Table 1 table1:** The list of trial centers.

Number	Institution	Prefecture
1	Ankou Medical Clinic	Tokyo
2	Ayano Clinic	Saitama
3	BOOCS Clinic Fukuoka	Fukuoka
4	Chuo Naika Clinic	Tokyo
5	Ebisu Garden Place Clinic	Tokyo
6	Higashi-hie Naika	Fukuoka
7	Hosoda Shinryojo (clinic)	Tokyo
8	Inoue Naika Clinic	Ibaraki
9	Kanda Clinic	Tokyo
10	Keio University Hospital	Tokyo
11	Kimura-Shiro Clinic	Fukuoka
12	Kita Shin-Yokohama Naika Clinic	Kanagawa
13	Mashiba Iin (clinic)	Saitama
14	Maekawa Medical Clinic	Kanagawa
15	Miyazaki RC Clinic	Tokyo
16	Motosumiyoshi Kokoromi Clinic	Kanagawa
17	Nakameguro Atlas Clinic	Tokyo
18	National Center for Global Health and Medicine	Tokyo
19	Nemoto Geka-Seikeigeka (clinic)	Saitama
20	Nihonbashi Naika-Allegy Clinic	Tokyo
21	Nomura Iin (clinic)	Tokyo
22	Odayaka Life Naika Clinic	Saitama
23	Saitama City Hospital	Saitama
24	Sawayama Naika-Sougoushinryou Clinic	Fukuoka
25	Segawa Hospital	Saitama
26	Shimizu Clinic Fusa	Saitama
27	Shinjuku Research Park Clinic	Tokyo
28	Sone Clinic Shinjuku	Tokyo
29	Tajima Clinic	Tokyo
30	Tenjin Sogo Clinic	Fukuoka
31	Ueda Naika Clinic	Fukuoka

### Intervention and Control

In addition to the 12-week standard treatment procedure for smoking cessation [5], we will prescribe the CASC to the treatment group. On the other hand, a control app will be prescribed to the control group. The standard 12-week smoking cessation treatment protocol provides 5 on-site examinations and in-person counseling by a primary physician at each outpatient clinic within 3 months.

CASC consists of a CureApp Smoking Cessation smartphone app based on a cloud system paired with a mobile CO checker for participants and a Web-based patient management software for primary care physicians. Participants in the treatment group will install the app in their smartphones and then begin taking a few minutes every day for watching a video tutorial regarding smoking cessation; in addition, participants from the treatment group will keep a digital diary of quitting smoking, chat with artificial intelligence (AI) nurse, and check their exhaled CO concentration by the mobile CO checker at least once a day. Physicians will be able to follow participants’ exhaled CO concentration data and physical conditions through a secure cloud system and review them during the clinic visits (Figure 2).

**Table 2 table2:** The trail assessment and evaluation schedule.

Assessments	Observational period							At withdrawal
	Day of registration (Day 1)	2 weeks (Day 15)	4 weeks (Day 29)	8 weeks (Day 57)	12 weeks (Day 85)	24 weeks (Day 169)	52 weeks (Day 366)	
Patients’ background	✓							
Tobacco Dependence Screener	✓							
Brinkman Index^a^	✓							
Fagaström Test for Nicotine Dependence	✓							
12-item French version of the Tobacco Craving Questionnaire	✓	✓	✓	✓	✓	✓	✓	
Kano Test for Social Nicotine Dependence	✓			✓	✓	✓	✓	
Mood and Physical Symptoms Scale	✓	✓	✓	✓	✓	✓	✓	
Exhaled carbon monoxide concentration	✓	✓	✓	✓	✓	✓	✓	✓
Status of nonsmoking	✓	✓	✓	✓	✓	✓	✓	✓
Status of device use		✓	✓	✓	✓	✓		✓
Adverse events	✓	✓	✓	✓	✓	✓	✓	✓

^a^Brinkman index=(number of cigarettes per day)×(number of smoking years).

Inclusion and exclusion criteria.Inclusion:Participants diagnosed with nicotine dependence (Tobacco Dependence Screener≥5 points)Participants with Brinkman index≥200Participants who wish to quit smoking immediatelyParticipants who agree to receive the smoking cessation treatment program and sign the written consent formParticipants who can use a smartphone (operating system: Android 5.0 and above or iPhone 8.0 and above)Exclusion:Participants with severe mental illnessParticipants who cannot come to their follow-up clinic visits during the 1 yearParticipants who have started taking a smoking cessation medication within 1 year before the registrationParticipants who plan to use any smoking cessation aids and participate in any kind of smoking cessation activities (not limited to smoking cessation therapy) outside the trialParticipants whose investigator or clinical trial doctor judged them to be unsuitable for participation in this trial owing to other reasons

On the other hand, participants from the control app group will be able to perform only 6 basic functions in their app as follows: (1) show the user guide (how to use the app); (2) enter their profile and set the start date of smoking cessation; (3) display the course of 5 visits during the 12-week treatment with a summary of objectives of each visit; (4) show the date of next appointment; (5) get the contact form for technical support; and (6) display an app version, privacy policy, and other administrative information. The other functions of the CASC app will not be incorporated in the control app. The control app will not include the mobile CO checker either. Note that exhaled CO concentrations will be measured by the medical staff at each clinic visit regardless of the study groups, and these CO data at the clinic will be used in the analysis of study outcomes.

**Figure 2 figure2:**
[figure not shown]
Overview of the "CureApp Smoking Cessation". CO: carbon monoxide; IoT: Internet of Things.

The CASC, control app, and mobile CO checker delivered by CureApp Inc. (Tokyo, Japan) should be carefully managed to ensure they are not used outside the clinical trial at each medical institution. A prescription code will be required to activate the investigational device, and the control group app will be issued by sponsors specific to each practicing medical institution; these sponsors regularly (at least once a year) perform inventory confirming there will be no usage of the app outside the trial.

### Overview of the “CureApp Smoking Cessation” Smartphone app

The CASC smartphone app was developed at CureApp Inc. supervised by the Division of Pulmonary Medicine, Department of Medicine, Keio University School of Medicine. The app runs on both iOS and Android smartphones. Primary physicians will provide the app prescription code to participants at their outpatient clinics. Participants will download the app through their smartphones, activate the app entering the code, and enter their baseline data including age, sex, years of smoking, number of cigarettes per day, prescribed medications (nicotine patch or varenicline), and motivation and self-confidence regarding smoking cessation. These data will be securely sent to the cloud storage, and the AI of our system will assemble tailor-made smoking cessation programs suitable to each participant based on their personal information. Personal data stored on the cloud can be reviewed by primary physicians. The CASC app has the following 4 main components to maximize the therapeutic effects of pharmacological therapy and counseling provided by health care professionals: (1) keeping a smoking cessation diary (once a day); (2) lectures and educational videos helping its users quit smoking; (3) interactive counseling by chat-bot (AI nurse); and (4) daily measurement and recording of exhaled CO concentration levels at home through a mobile CO checker.

Regarding a Web-based personal computer software for primary doctors, it provides a data management app from patients’ CASC mobile apps and advice for physicians to follow the national clinical guidelines appropriately.

### Outcomes

The primary outcome of this study will be the biochemically validated CAR from weeks 9-24. The success of smoking cessation has been defined as (1) self-reported continuous abstinence from weeks 9-24 and (2) exhaled CO concentration no more than 10 ppm at both weeks 12 and 24. In current smoking cessation programs, the CAR from weeks 13-24 drastically decreases, whereas our investigational device is expected to prevent this reduction by covering “treatment gaps” to promote the retention of appropriate recognition and behavioral changes. A single-arm prospective pilot study showed that a CASC app, even without a mobile CO checker, had a significantly higher CAR from weeks 9-24 than the historical cohort that had received standard smoking cessation program [16,17].

In addition, we will evaluate the following secondary outcomes: (1) 7-day point prevalence abstinence at weeks 4, 8, 12, 24, and 52; (2) the CAR from weeks 9-12 and from weeks 9-52; (3) changes in several scores related to smoking cessation, including the Mood and Physical Symptoms Scale (MPSS) [18], 12-item French version of the Tobacco Craving Questionnaire translated into Japanese (FTCQ-12) [19], Kano Test for Social Nicotine Dependence (KTSND) [20], and time to first lapse after initial visit; (4) usage rates of smartphone apps; and (5) the presence of product problems or adverse events.

### Follow-Up Schedule

Table 2 shows the overall follow-up schedule of this trial. At registration, patients’ background profile, exhaled CO concentration, nicotine dependence, and smoking status will be assessed using instruments such as the Tobacco Dependence Screener [21], Brinkman index (multiplied by cigarettes per day and years of smoking), Fagerström Test for Nicotine Dependence (FTND), FTCQ-12, KTSND, and MPSS. The background profile includes age, sex, body weight, years of smoking, cigarettes per day, and medical history at the initiation of device use. Regular follow-up visits will be scheduled at 2 weeks (±7 days), 4 weeks (±7 days), 8 weeks (±14 days), 12 weeks (±14 days), 24 weeks (±28 days), and 52 weeks (±28 days); during these follow-up visits, we will examine patients’ scores regarding FTCQ-12, KTSND (after 8 weeks), and MPSS, as well as exhaled CO concentration, status of nonsmoking, status of device use, and adverse events. Adverse events and concomitant pharmacological therapy will be recorded through the trial.

An independent monitoring staff will conduct on-site data monitoring. In addition, the staff will review trial database to confirm whether principal and subinvestigators at each clinic perform the clinical trial according to the research proposal and standard operation procedures, and data queries will be asked if necessary.

### Participant Withdrawal Criteria

Participants will be discontinued from follow-up visits for this trial when they meet either of the following criteria: (1) participants request discontinuation; (2) researchers consider discontinuation is necessary owing to severe adverse effects, for example; (3) the eligibility criteria was violated; (4) significant deviation from the protocol occurred; (5) study institution terminated trial participation because of good clinical practice violation, for example; (6) participants’ further follow-up visits are considered very difficult to accomplish; (7) continuing smoking even at the 9^th^ week or participant no longer intends to continue the smoking cessation program; (8) sponsor cannot continue the trial; and (9) any other cause in which researchers decide discontinuation is appropriate.

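### When a researcher discontinues a participant for a severe adverse effect, follow-up visits end, so later safety and abstinence data are lost for anyone still willing and able to attend

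*Protocol article*

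**What the plan says.** All places are in the protocol article.

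- **Participant Withdrawal Criteria.** One lead sentence governs nine criteria: "Participants will be discontinued from follow-up visits for this trial when they meet either of the following criteria". The second is "2) researchers consider discontinuation is necessary owing to severe adverse effects, for example". The first covers participants who ask to stop. The sixth covers those whose "further follow-up visits are considered very difficult to accomplish". The ninth lets researchers discontinue for any other cause they think appropriate.
- **Table 2.** Adverse events, exhaled CO and nonsmoking status are ticked at every visit to week 52. A separate column, "At withdrawal", is ticked for exhaled CO, nonsmoking status, device use and adverse events.
- **Treatment duration.** The Abstract (Methods) says "Both groups will receive a 12-week standard smoking cessation program with pharmacotherapy and counseling". Overall Trial Design says "The treatment group will use the CASC smartphone app integrated with a mobile CO checker and a Web-based patient management software for 24 weeks".
- **Outcomes.** Primary success needs self-reported continuous abstinence over weeks 9-24 and "exhaled CO concentration no more than 10 ppm at both weeks 12 and 24". Adverse events are a secondary outcome.
- **Follow-Up Schedule.** "Adverse events and concomitant pharmacological therapy will be recorded through the trial".
- **Statistical Analysis.** All analyses follow the intention-to-treat principle.

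**The concern.** A severe adverse effect may call for stopping varenicline, the patch or the app. It need not be a reason to stop seeing the participant. The lead sentence joins the two: once the researcher uses criterion (2), visits end.

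Two things are at stake for a participant who would still have come. First, an intention-to-treat analysis needs the week 12 and week 24 CO readings and the smoking history from every randomized person. Here, any that remain would have to be handled by a missing-data rule when they could have been observed. Second, the article promises adverse event recording through the trial, but a person withdrawn for a severe event has no later scheduled point at which further events would be collected.

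**Working it through.** **Does the design need people on treatment in order to follow them?** No. The standard program lasts 12 weeks and CASC use 24 weeks, yet Table 2 schedules visits to week 52. Being off treatment is already an ordinary state for a followed participant.

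**What one affected participant loses.** The nominal Table 2 days are 1, 15, 29, 57, 85, 169 and 366. The primary CO checks fall on Days 85 and 169. The point-prevalence time points are weeks 4, 8, 12, 24 and 52. Withdrawal at a visit is taken to mean that visit's data are obtained. Days lost = 169 or 366 minus the day of withdrawal.

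| Withdrawn | Visits lost (of 6) | Primary CO checks lost (of 2) | Point-prevalence points lost (of 5) | Days lost to Day 169 | Days lost to Day 366 |
|---|---|---|---|---|---|
| Before week 2 | 6 | 2 | 5 | up to 168 | up to 365 |
| Week 2 | 5 | 2 | 5 | 154 | 351 |
| Week 4 | 4 | 2 | 4 | 140 | 337 |
| Week 8 | 3 | 2 | 3 | 112 | 309 |
| Week 12 | 2 | 1 | 2 | 84 | 281 |
| Week 24 | 1 | 0 | 1 | 0 | 197 |

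The assessment at withdrawal adds one reading when the participant leaves. It does not replace the later ones.

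**The plan's own sample size.** Inputs from Sample Size: 52.8% v 40.8%, 290 per arm, 80% power, chi-square test, 2-sided .05.

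- n = [1.96√(2p̄q̄) + 0.842√(p₁q₁ + p₂q₂)]² / δ², with p̄ = 0.468 and δ = 0.12. This gives 271 per arm without continuity correction and 287 with it. The stated 290 is consistent with the corrected test and is not disputed.
- Power at 290 = Φ{[δ√n − 1.96√(2p̄q̄)] / √(p₁q₁ + p₂q₂)}, uncorrected. With the numbers in: Φ{[2.044 − 1.383] / 0.701} = 82.7%.

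**Trial-level illustration.** No rate of criterion (2) withdrawal is given. The shares w below are assumptions, equal in both arms. Counting as failures multiplies both rates by (1 − w); excluding reduces n to 290(1 − w).

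| Assumed w | About per arm | Rates if counted as failures | Difference | Power, as failures | Power, if excluded |
|---|---|---|---|---|---|
| 0 | 0 | 52.8% v 40.8% | 12.0 | 82.7% | 82.7% |
| 1% | 3 | 52.3% v 40.4% | 11.9 | 82.0% | 82.3% |
| 5% | 15 | 50.2% v 38.8% | 11.4 | 79.0% | 80.8% |

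One participant is 1/290 = 0.34 percentage points of an arm's abstinence rate.

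**The case against.** The case against has five parts.

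- **Discretion.** Criterion (2) applies only when a researcher judges discontinuation necessary. Nothing says that stopping a drug or the app counts as discontinuation, so a researcher could stop treatment and keep the participant on schedule without breaking a stated rule. This stands as a limit on how often the problem arises. A reader might infer that any severe adverse effect removes the participant automatically; the text does not say so. Once the criterion is used, however, the end of visits follows from the lead sentence.
- **The withdrawal assessment.** A reader might infer that the end of visits is the only thing that happens. Table 2 contradicts that with its closing assessment. What remains is the loss after that date.
- **Who is affected.** Criteria (1) and (6) already cover people who will not or cannot attend, so it is tempting to conclude that criterion (2) adds only people who would have come. That is inference. The criteria can overlap: a participant in hospital could meet both (2) and (6). The point holds only for those still willing and able.
- **A condensed article.** Follow-up of the triggering event to resolution may be in the full protocol and is not part of this point. Missing-data handling belongs to the analysis plan, which is not shown, so counting as failures is an assumption. Neither removes the rule that the article states.
- **Size.** The participants are described as otherwise healthy, and the documents give no basis for a share as high as 5%. This stands.

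**Conclusion.** The point holds as an avoidable loss of data, not as an error in the analysis. The article makes the end of follow-up visits the consequence of discontinuation under criterion (2) and states no route by which a willing participant stays on schedule off treatment. An affected person withdrawn by week 8 loses both primary CO checks; one withdrawn at week 12 loses the week 24 check. All lose scheduled adverse event collection after they leave.

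Across the trial the effect is small unless such withdrawals are common: at assumed equal shares of 1% to 5%, power is 82.0% to 79.0% if they count as failures, or 82.3% to 80.8% if excluded. The failure figures also assume that those withdrawn would otherwise have quit at the same rate as the rest of their arm.

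A reader might infer bias between arms. If 5% were lost in the CASC arm alone and counted as failures, the difference would be 9.4 points (0.95 × 52.8 − 40.8) and power 62.0%. Nothing in the documents suggests so unequal a loss, and no direction of bias is claimed. This is an optional, inexpensive improvement.

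**What to change.** Amend the lead sentence and criterion (2) together:

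- When a researcher judges discontinuation necessary for an adverse effect, the app and/or medication is stopped. The participant stays on the Table 2 schedule for adverse events, exhaled CO and smoking status.
- Exceptions: consent is withdrawn, or the researcher judges that attending is itself medically inadvisable or not feasible. This keeps clinical discretion.
- Apply the same rule where criterion (9) is used for an adverse effect; otherwise it remains another route off visits.
- Keep the assessment at withdrawal for those who do leave.

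The cost is a short wording amendment. The visits, and the 10,000 yen payment for each of 7 visits, are already planned for every participant. At most 6 visits per affected participant are kept: 6 × 10,000 = 60,000 yen, or 6 / (580 × 7) = 6 / 4,060 = 0.15% of planned visits. For withdrawal at the week 2 visit it is 5 visits, 50,000 yen.

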### Statistical Analysis

All statistical analyses will be performed according to the intention-to-treat principle and using 2-sided at a .05 significance level. The baseline characteristics will be described by the mean and SD, median and quantiles (continuous variables), or proportion (categorical variables). We will examine the outcomes using the full analysis set. For the primary outcome, we will compare CARs from weeks 9-24 comparing the CASC treatment group and the control group using a logistic regression model adjusted for prescribed smoking cessation medications. In addition, secondary outcomes at each defined period will be evaluated with logistic regression analysis adjusted for appropriate covariates between the groups. We will provide descriptive statistics, odds ratios, 95% CIs, and *P* values for each outcome. A statistical analysis plan detailing all statistical computations will be completed prior to the lock of the database. SAS statistical software, version 9.4 or upper version (SAS Institute Inc), will be used for all the analyses.

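### Follow-up visits, not only device use, end for eligibility violations, protocol deviations and researcher discretion, so primary outcomes that intention to treat needs are lost although they could be collected.

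*Protocol article*

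**What the plan says.** The Participant Withdrawal Criteria section of the protocol article opens: "Participants will be discontinued from follow-up visits for this trial when they meet either of the following criteria". What ends is the visits, not merely use of the app or the cessation program. Of the nine listed grounds, the third and fourth read "3) the eligibility criteria was violated; (4) significant deviation from the protocol occurred", and the last is "any other cause in which researchers decide discontinuation is appropriate". Criterion (6) covers people whose further visits are thought very hard to achieve. Criterion (7) covers people still smoking at week 9 and the case where a "participant no longer intends to continue the smoking cessation program".

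The Statistical Analysis section states: "All statistical analyses will be performed according to the intention-to-treat principle". It adds: "We will examine the outcomes using the full analysis set". The details are left to a statistical analysis plan that is not shown.

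The Outcomes section defines primary success as self-reported continuous abstinence over weeks 9-24 together with exhaled CO of at most 10 ppm at week 12 and again at week 24. Table 2 has an at-withdrawal column with exhaled CO and nonsmoking status.

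The trial is open-label (Overall Trial Design). Under Intervention and Control, CASC participants watch tutorials, keep a diary, chat with the AI nurse and "check their exhaled CO concentration by the mobile CO checker at least once a day". The control app has six basic functions and no CO checker.

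**The concern.** Intention to treat depends on outcome data as much as on the analysis. It needs the outcome of each randomised participant whatever happened after allocation. Criteria (3), (4) and (9) act after randomisation: an eligibility violation comes to light, a deviation is judged significant, or a researcher decides that stopping is appropriate. None of these makes the week 12 or week 24 outcome unobtainable. The rule nevertheless stops the visits at which that outcome would be measured.

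Success needs both clinic readings, so an abstinent participant discontinued before week 24 must be counted as a smoker, imputed or left out. No analysis rule can recover a reading that was never taken.

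The researchers know the arm when they apply criteria (4), (6) and (9). If the loss differs by arm, it biases the primary comparison. If it is equal, it costs power. The Sample Size section mentions no allowance for either.

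**Working it through.** **Reading the sections together**

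1. Participant Withdrawal Criteria: visits stop on the listed grounds.
2. Outcomes: success needs clinic CO at weeks 12 and 24.
3. From 1 and 2, discontinuation before week 24 rules out a demonstrated success. The at-withdrawal reading in Table 2 gives status on the day of leaving and does not replace the week-24 reading.
4. Statistical Analysis: everything follows intention to treat. The data-collection rule therefore removes information that the analysis principle calls for.

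**Inputs**

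From the Sample Size section: 52.8% (CASC) and 40.8% (control), 290 per arm, chi-square test, two-sided 0.05, 80% power. The discontinuation rates below are assumptions, because the article gives none. Counting the discontinued as smokers is also an assumption, because the article states no missing-data rule.

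**Reproducing the plan's figure**

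n = [1.96 × √(2p̄(1−p̄)) + 0.8416 × √(p₁(1−p₁) + p₂(1−p₂))]² / (p₁−p₂)², with p̄ = 0.468. This gives 271 per arm without continuity correction and 287 with it, against 290 stated. Power at 290 is 82.7% uncorrected and 80.5% corrected. The stated size is reproduced with the correction and has almost no reserve. The uncorrected test is used below.

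**Effect of losing would-be abstainers**

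If a fraction w of the would-be abstainers in an arm is discontinued before week 24 and counted as smokers, the observed rate is p(1−w). A loss of 5% is 0.05 × 0.528 × 290 ≈ 8 people in CASC and 0.05 × 0.408 × 290 ≈ 6 in control.

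Power = Φ[(d − 1.96 × SE₀)/SE₁], where d is the observed difference, SE₀ = √(2p̄(1−p̄)/290) and SE₁ = √((p₁(1−p₁) + p₂(1−p₂))/290).

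| Would-be abstainers lost | CASC | Control | Difference (points) | Power |
|---|---|---|---|---|
| None | 52.8% | 40.8% | 12.0 | 82.7% |
| 5% in both arms | 50.2% | 38.8% | 11.4 | 79.0% |
| 10% in both arms | 47.5% | 36.7% | 10.8 | 75.1% |
| 5% in CASC only | 50.2% | 40.8% | 9.4 | 62% |
| 10% in CASC only | 47.5% | 40.8% | 6.7 | 37% |
| 5% in control only | 52.8% | 38.8% | 14.0 | 93% |

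For the fourth row: 0.528 × 0.95 = 0.5016 and d = 0.0936. SE₀ = 0.04135 and SE₁ = 0.04117, so (0.0936 − 1.96 × 0.04135)/0.04117 ≈ 0.305 and Φ(0.305) ≈ 0.62.

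**Under no true effect (40.8% in both arms)**

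- Equal loss: no bias, and type I error stays at 5.0%.
- 5% lost in one arm only: 0.408 × 0.05 = 2.0 points of bias, with type I error about 7.9%.
- 10% lost in one arm only: 4.1 points of bias, with type I error about 17.2%.

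**The case against.** The strongest reply is that the two sections do not strictly contradict each other. The withdrawal criteria stop visits and exclude nobody from the analysis. Discontinued participants can stay in their assigned arm under a missing-outcome rule, and the analysis plan may say so. This stands. A reader might infer that these people are dropped from the analysis, but the article does not say that. The definition of the full analysis set and the missing-data rule properly belong to the analysis plan. What the reply does not meet is that no analysis plan can restore visits that the protocol has stopped.

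A reader might also infer that the rule acts unequally, and against CASC, because that arm has more daily tasks from which to deviate. The documents do not support this as a fact. Nothing says that a missed diary entry or CO check is a significant deviation. App usage is a secondary outcome, so low use is something to be measured. The opposite direction is also plausible: control participants who know that they have the reduced app may seek outside cessation aids, and people planning to use those are excluded at entry. Eligibility itself is fixed before allocation. Unequal loss is therefore possible, but its direction and size are unknown.

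The one-arm power figures are extreme cases. They also assume that the people lost would have abstained. Counting a discontinued participant who would have smoked anyway as a smoker changes nothing.

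The at-withdrawal assessment deserves credit, although it cannot serve as the week-24 reading. Criterion (7) looks like the ground most closely tied to the outcome, but a person still smoking at week 9 has already failed the primary outcome. The loss there falls on later point prevalence and the score outcomes.

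**Conclusion.** The concern holds in a limited form. The protocol article stops outcome collection for reasons that intention to treat should ignore, partly at the discretion of researchers who know the arm. A participant stopped before week 24 cannot then be shown to meet the primary definition of success.

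The size depends on discontinuation rates that the documents do not give. With equal loss the harm is modest: about 4 points of power at an assumed 5% (82.7 − 79.0 = 3.7) and no inflation of type I error. With loss in one arm only it is material: 62% power if 5% is lost in CASC alone, or type I error of about 7.9% under no true effect. All these figures assume that the discontinued are would-be abstainers counted as smokers.

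The point should be fixed, but it is not a fatal defect: no differential withdrawal and no exclusion from analysis is documented.

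**What to change.** Reconcile the Participant Withdrawal Criteria with the Statistical Analysis section by separating two events: the end of device or program use, and the end of outcome follow-up.

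- State that criteria (3), (4) and (9) do not end outcome collection.
- State that smoking status and clinic CO at the already scheduled week 12, 24 and 52 visits are still sought from all randomised participants who have not withdrawn consent and whose site remains open. This includes those discontinued under (2), if they still consent.
- Under (6), collect these data where feasible, since wording cannot make an impracticable visit practicable.
- Under (7), also seek the later point-prevalence data, even though smoking at week 9 already settles the primary outcome.

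Decisions on stopping treatment or device use are left as they are.

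The cost is amendment wording and a few retained visits that are already in the schedule. The 290 per arm and the stated power need no change on this account if follow-up is kept.
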